### Recruitment of cooperation partners and young cannabis users

Subjects for the study are recruited by cooperating institutions from the settings mentioned above. These cooperation partners were trained by the study group to identify incoming clientele for their eligibility to participate at the study, to perform motivating take-in talks to these young cannabis users, and to gather data for the first two points of measurement (pre and post). The follow-up measurement will be performed by the study group. Moreover, staff of the cooperation partners is instructed to perform the CAN Stop training.

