In a first attempt to identify suitable cooperation partners, we systematically scanned comprehensive help provision and therapy guides of Northern and Eastern Germany as well as the Internet for institutions. All identified institutions were then invited to participate at the study with an information letter and asked to fax back an attached reply form together with a questionnaire about structural and work details of the institution, such as number of incoming young cannabis users in the targeted age range and number of staff. Prior to this, a target number of cooperation partners needed to gather the subjects was calculated on the basis of a power calculation, an estimated attrition rate of 50% and under the premise that CAN Stop training groups should be composed of six to ten group participants. If feedback was not given within six weeks after letters were sent out, a study group member called to check back with the institution. An exception from this procedure was made within the setting of juvenile prisons: because their total number was rather low, their staffs were contacted directly via phone calls. The response rate varied between different settings between 57% in juvenile prisons, 10% in in-patient medical clinics, 5% in out-patient medical clinics and 5% in the youth welfare and drug addiction aid. If institutions signalled to be in contact with young cannabis users in their daily routines and were interested in study participatioin, a study group member gave a presentation of the project and invited institutions to participate at the study. In sum, we could aquire a total of 11 cooperation partners within the youth welfare and drug addiction aid, 9 cooperation partners of the out-patient medical system, 8 cooperation partners of the in-patient medical system and 3 participating prisons for juvenile offenders. Participating cooperation partners were randomly assigned to perform the CAN Stop intervention plus their usual treatment as an intervention group or to provide for control group subjects, who received the cooperation partner's previously installed treatment as usual (TAU). As for other treatments, provided by the different institutions (besides CAN Stop), cooperation partners differed in their usually provided routines depending on their specific setting. While most prisons indicated, other kinds of therapy besides CAN Stop were rather limited and merely consisted of counselling talks or conceptual work within the organizational framework of the prison, the in-patient medical system's cooperation partners of course provided many other facets of treatment - to mention both extremes of this varying continuum. Institutions, which indicated they were already participating in other structured programmes similar to CAN Stop were excluded from the study in order not to compare CAN Stop with eventually competing studies (e.g. FrED, see above).

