
Recruitment for subjects was performed by cooperation partners within their daily work routines. In addition, the study group provided for flyers, which gave information on the study, its objectives and the group training to recruit participants. Young cannabis users interested in the programme were asked to contact a centralized telephone hotline installed by the study group to provide for a first check-up of inclusion criteria, to inform about the study and then to randomly allocate subjects to wait list control groups or to intervention groups in respective institutions. Young cannabis users in prisons are exempted from this procedure, because a random allocation of prisoners is not possible: the juidical allocation of young offenders into the prisons will decide about whether they are selected into a prison performing an intervention or a control group, their inclusion criteria are checked in in-take talks. Inclusion criteria were (1) the participants' age between 14 and 21 years, (2) a cannabis consume, which is deemed problematic by the young cannabis user or significant persons in his or her context (e.g. parents, teachers) (3) the participant's willingness to at least think over previous consumption patterns and to participate at a group dealing with the topic and (4) the informed consent of participants and in the case of underage participants the informed consent of a parent or official guardian. Young cannabis users were excluded from the study when they showed acute symptoms of psychosis or suicidality. Both of these exclusion criteria were checked via standardized screening questions at the beginning of the face-to-face take-in talks at the respective cooperation partner's institutions. Young cannabis users were invited to participate at the study regardless of whether their access to cooperating institutions was initiated by the cannabis users themselves or whether pressure was exerted by e.g. school, employers or because of a judicial condition of probation, however, this is documented and will be integrated into outcome analyses.

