### Measures

Young cannabis users participating at the study were asked to fill in several measures to assess target variables. Table 1 gives an overview of measures used.

**Table 1 T1:** Measures for young cannabis users

Target variable	Measure	Point of measurement
Sociodemographics Living situation Social network Problems with school, police, debts... Education Prior counselling and therapies		pre, follow-up
Screening for acute psychosis	Subscale of the Diagnostisches Interview psychischer Störungen (DIPS; Diagnostic Interview of psychiatric disorders) [26]	pre
Substance use history	Following the assessment standards III of the DG-Sucht (German Society for Addiction Research and Therapy)	pre, post, follow-up
Severity of dependence	Severity of dependence scale (SDS) [27]	pre, post, follow-up
Psychosocial adjustment	Youth self report (participants aged 14-17) [28] Young adult self report (Participants aged 18-21) [29]	pre, post, follow-up
Expected positive and negative effects of cannabis use	Comprehensive Cannabis Expectancy Questionnaire (CCEQ) [30]	pre, post, follow-up
Relationship to friends and peers	Questionnaire for health-related quality of life (Kiddo-KINDL revised, subscale "friends") [31]	pre, post, follow-up
Family relationships	Familienbogen/Selbstbeurteilungsbogen (family inventory, self-rating) [32]	pre
Motivation for change in cannabis use	Fragebogen zur Erfassung der Veränderungsbereitschaft (FEVER; Questionnaire to protocol the willingness for change) [33,34]	pre, post, follow-up
Personal goals with regard to changes in substance use	Zielskala [35]	pre, post, follow-up
Self-efficacy with regard to cannabis abstinence or limited cannabis use	Heidelberger Skalen zur Abstinenz-/Kontrollzuversicht (HEISA-16/HEIS-KOTZ-12; Heidelberg scales of confidence regarding abstinence/controlled use) [35]	pre, post, follow-up
Satisfaction with the training	Fragebogen zur Beurteilung der Behandlung, Version Patient (FBB-P; Questionnaire for the satisfaction with treatment, patient version) with minor adaptations [36]	post
Peer resistance regarding cannabis use	own development	pre, post, follow-up

In addition, trainers were asked to answer a short questionnaire about themselves prior to t0 in order to gather data for analysing possible trainer effects in secondary analyses. This included their professional background, own beliefs and attitudes towards cannabis use and personality characteristics, using the Big Five Inventory-10 (BFI-10) [25].

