### Measures against bias

The study is unblinded with regard to trainers, who hand out the questionnaires at t0 and t1 measurements to the clients. However, t2 telephone interviewers are blind to whether participants belonged to a control or intervention group. A problem of the study may be different selection effects in the groups. Participants of the study may be inclined to follow through a regular training as opposed to potentially less structured treatment as usual. In order to estimate this kind of bias we will analyze models to predict drop-outs in both, the intervention and the control group. In order to prevent trainers from using CAN Stop training elements in their working routine and to unintentionally blur TAU and CAN Stop interventions, trainers of institutions, who were selected into the control group will receive their training for the CAN Stop training intervention only after they completed t1 measurements in young cannabis users. Supervision protocols of CAN Stop trainers for later qualitative analyses will be handled in a way that no inference can be made about the respective trainer.

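### Staff who know the arm apply the exclusion screen and take t0 data after hotline allocation (prisons aside), and in all settings unblinded staff gather the t1 self-reports, so entry and t1 reporting can differ by arm

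*Protocol article*

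**What the plan says.** The section on recruitment of cooperation partners and young cannabis users describes the path into the study. Interested users phone a hotline run by the study group. Its tasks are a first check of the inclusion criteria and then "to inform about the study and then to randomly allocate subjects to wait list control groups or to intervention groups in respective institutions". The two exclusion criteria, acute psychosis and suicidality, come later: "Both of these exclusion criteria were checked via standardized screening questions at the beginning of the face-to-face take-in talks". The same sentence places those talks at the cooperating institutions. Table 1 (Measures) lists "Screening for acute psychosis" as a pre measure.

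Institution staff are trained "to perform motivating take-in talks to these young cannabis users, and to gather data for the first two points of measurement", that is, pre and post. Institutions themselves carry one condition: "Participating cooperation partners were randomly assigned to perform the CAN Stop intervention plus their usual treatment as an intervention group", or else to supply controls on usual treatment. Prisons are exempt from the hotline; judicial placement decides the arm there.

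On blinding, the section on measures against bias states: "The study is unblinded with regard to trainers, who hand out the questionnaires at t0 and t1 measurements to the clients". Only the t2 telephone interviewers are described as blind. Under Study Design and Setting, the post measurement consists of questionnaires alone. The Analysis section plans an intention-to-treat comparison by ANCOVA, with cannabis use at t0 as covariate.

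**The concern.** There are two separate openings for bias.

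**Entry.** If people are screened out, decline or fail to appear after allocation, and the staff involved know the arm, the two groups that reach t0 need not be comparable. The t0 value used for adjustment is also taken after allocation. The incentives are not the same in both arms. A completed training cycle pays 400€, groups need six to ten members, and a group stops at three or fewer. Intervention sites therefore have an immediate reason to enrol and keep people that control sites do not share at that stage.

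**Outcome at t1.** Cannabis use and abstinence self-efficacy are self-reported, and Table 1 lists no biological measure. Intervention participants may return their forms to the person who has just led eight sessions on these two topics. Control participants return theirs to staff not yet trained in CAN Stop. If this changes how people answer, the change enters the treatment effect directly. It would also blur the comparison of t1 with t2, because collection moves from unblinded staff to blinded interviewers.

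**Working it through.** The plan gives no figure on this point, so the check is mainly one of sequence.

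**Order of steps outside prisons**

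| Step | Who | Arm known to that person? |
|---|---|---|
| First check of inclusion criteria, then random allocation | Hotline, study group | Allocation made here |
| Psychosis and suicidality screen | Staff of the assigned institution | Yes, one condition per institution |
| t0 interview and questionnaires | Staff of the assigned institution | Yes |
| t1 questionnaires | Trainers or staff of the institution | Yes, stated openly |
| t2 telephone interview | Study group | No, stated as blind |

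Written consent, with a guardian's for minors, is an inclusion criterion, and Ethical considerations limits the analysis to people who gave it. A telephone call cannot itself supply written consent, so consent probably also follows allocation. That is an inference; the article does not date it.

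The order of allocation and screening rests on the words joining the hotline's tasks and on the place of the take-in talk. The Discussion allows that some users will have met an institution before calling, but it does not move the screen ahead of allocation.

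**Do the stated safeguards reach the problem?** The section on measures against bias offers drop-out models by group, delayed CAN Stop training for control staff, and blinded t2 interviewers. The first concerns loss of participants, the second contamination and the third the follow-up. None covers exclusion after allocation or the way t1 answers are collected. The hypotheses in the Background and Analysis sections concern levels after the training, which most naturally means t1.

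**Scale, on assumed biases.** Inputs from the Analysis section: f = 0.25, n = 119, α = 0.05. The biases are assumptions, not figures from the documents.

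- For two equal groups d = 2f = 2 × 0.25 = 0.5.
- Share of the planned effect: 0.1/0.5 = 20%; 0.2/0.5 = 40%.
- With 119 analysed in two equal arms and no clustering, SE = √(4/119) = 0.183 SD.
- With no true effect, the two-sided false-positive rate is 1 − Φ(1.96 − b/SE) + Φ(−1.96 − b/SE):

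| Assumed differential bias b (SD) | b/SE | False-positive rate |
|---|---|---|
| 0 | 0 | 5% |
| 0.1 | 0.55 | about 8% |
| 0.2 | 1.09 | about 19% |
| 0.3 | 1.64 | about 37% |

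Clustering would widen the SE and lower these rates; covariate adjustment would narrow it and raise them. A larger sample does not remove such a bias. For differential entry no calculation is possible, because the article gives no expected number of exclusions or refusals.

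**The case against.** The case for the plan is substantial.

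- Only two criteria are screened after allocation, with standardised questions and a diagnostic-interview subscale for psychosis. A reader might infer that this undoes the randomisation. The documents do not support that: discretion is narrow and no rate of exclusion is given. It can weaken comparability, no more.
- A reader might infer that t1 reporting is biased in the intervention arm only. Control participants also return their forms to staff of the institution treating them, so any bias is the difference between two pressures, and its size is unknown. The ban on cannabis in prisons applies in both arms and does not by itself create a difference.
- A reader might infer a conflict with intention-to-treat. The article is silent on people excluded after allocation, and that detail commonly sits in a fuller document. Silence is not a contradiction.
- At t1 staff hand out forms; they do not interview or rate. The route by which forms come back is not described in detail.
- t0 is taken before training begins, so the covariate is still a pre-treatment measure.
- The lack of blinding is disclosed, selection effects are named as a problem, and a pragmatic design with one arm per institution makes staff awareness unavoidable.

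All of this stands and limits the claim. It does not answer the remaining point: the order of steps leaves entry open to knowledge of the arm, and the t1 comparison has no protection against differential reporting, although simple protection is available.

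**Conclusion.** The point holds in a limited form. Outside prisons, the exclusion screen and t0 follow allocation and are done by staff who know the arm, so entry and the baseline covariate can differ between arms. In all settings, t1 self-reports are handed out and gathered by unblinded staff, so reporting can differ between arms at the time point the hypotheses address. The part about the hotline does not apply to prisons, where individuals are not randomised.

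The size is unknown. The 20 to 40% share and the false-positive rates show only what biases of the assumed size would do. The conclusion rests on reading the hotline allocation as preceding the take-in talk, which is the plain sense of the text. This is a low-cost improvement to a disclosed design choice and does not invalidate the trial.

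**What to change.** 1. Have participants complete the t1 questionnaires themselves, seal them and send them unopened to the study group. Do the same for the questionnaire part of t0. The safety screening answers stay with the staff who need them. This applies in all settings, prisons included.
2. Where consent arrangements allow, put the standardised exclusion questions before the allocation is drawn, or at least before it is disclosed. Keep the face-to-face safety check as it is. Moving t0 data into the call is harder, because the data may be used only with written consent, and minors need a guardian's.
3. State that consenting participants allocated by the hotline are analysed in their allocated arm.
4. Report exclusions, refusals and no-shows after allocation by arm. This matters because an analysis set restricted to those who consent still depends on consent that may follow allocation.

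The cost is envelopes and postage, and a somewhat longer hotline call. Items 1, 3 and 4 can be adopted after recruitment has begun. Sealed return reduces the pressure of reporting to one's own trainer; it does not blind the participant, so some differential reporting may remain and should be acknowledged when t1 results are interpreted.

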### Intervention: The CAN Stop group training

The CAN Stop group training consists of eight group sessions à 90 minutes. Groups consist of six to ten young cannabis users and one or two trainers. The group contents and its timeline is described in a detailed manual. Moreover, a general introductory section of the manual provides trainers with background knowledge about cannabis, its effects, aspects of group dynamic as well as recommendations regarding the trainer's attitude towards participants and their consumption. The training's rationale is based on behavioural therapeutic and motivational interviewing elements [24]. It encompasses consumer or craving diaries, the work with social and emotional context variables and potential triggers as well as the elaboration of alternative behaviour strategies and the activation of participants' resources. Generally and for motivational reasons, it is left open to participants within the training whether they want to reduce or stop their cannabis use. However, certain settings at which the training is tested officially require absolute consume stops (e.g. prisons), yet this is a characteristic of the respective institution and not of the training itself. A more detailed description of the training is in preparation. After completing the CAN Stop training, certificates are handed out to participants who, participated at least at five out of eight group training sessions, for further gratification. If within a group, only three or less participants remain after other participants dropped out of the group, the group is not further continued.

### Training of CAN Stop trainers

The CAN Stop training is performed by cooperation partners' staff. Their professional background may vary starkly with regard to their therapeutical expertise. In order to empower cooperation partners' staff for performing the training, motivating take-in talks and procedures for data gathering, a detailed training is set up, which every trainer has to undergo beforehand. As an effect, our study's goal in essence is, not only to test the effect of the CAN Stop training but also to test the approach to empower cooperations partners' staff to perform the training. Several measures are taken to provide for a sufficient quality assurance with regard to the provision of the CAN Stop training. CAN Stop trainers are asked to record each session on videotape. Videotapes will later be used to check for trainers' adherence to the manual. A special adherence measure was developed, which is oriented closely to the training contents of each session. Regular supervision phone calls with trainers are made by the study group to ensure trainers feel comfortable with their CAN Stop training delivery, and trainers are invited to phone the study group if questions arise, be it regarding contents or regarding difficult social situations within the training or when training participants show signs of acute psychosis or suicidality. Notes are taken of these supervision talks for later qualitative analyses. Identification of these problems and recommendations about how to deal with them are also part of the training of trainers. For further control with regard to the young cannabis users, participants' comfort with the training, participants are asked to indicate their mood shortly at the beginning and end of each training sessions with colour-coded cards. Moreover, participants give feedback on the respective session at the end of each CAN Stop training session with regard to their satisfaction with the training contents and the atmosphere in the group. These data will be gathered and monitored by the study group to ensure that no CAN Stop training runs out of hand.

### Measures

Young cannabis users participating at the study were asked to fill in several measures to assess target variables. Table 1 gives an overview of measures used.

**Table 1 T1:** Measures for young cannabis users

Target variable	Measure	Point of measurement
Sociodemographics Living situation Social network Problems with school, police, debts... Education Prior counselling and therapies		pre, follow-up
Screening for acute psychosis	Subscale of the Diagnostisches Interview psychischer Störungen (DIPS; Diagnostic Interview of psychiatric disorders) [26]	pre
Substance use history	Following the assessment standards III of the DG-Sucht (German Society for Addiction Research and Therapy)	pre, post, follow-up
Severity of dependence	Severity of dependence scale (SDS) [27]	pre, post, follow-up
Psychosocial adjustment	Youth self report (participants aged 14-17) [28] Young adult self report (Participants aged 18-21) [29]	pre, post, follow-up
Expected positive and negative effects of cannabis use	Comprehensive Cannabis Expectancy Questionnaire (CCEQ) [30]	pre, post, follow-up
Relationship to friends and peers	Questionnaire for health-related quality of life (Kiddo-KINDL revised, subscale "friends") [31]	pre, post, follow-up
Family relationships	Familienbogen/Selbstbeurteilungsbogen (family inventory, self-rating) [32]	pre
Motivation for change in cannabis use	Fragebogen zur Erfassung der Veränderungsbereitschaft (FEVER; Questionnaire to protocol the willingness for change) [33,34]	pre, post, follow-up
Personal goals with regard to changes in substance use	Zielskala [35]	pre, post, follow-up
Self-efficacy with regard to cannabis abstinence or limited cannabis use	Heidelberger Skalen zur Abstinenz-/Kontrollzuversicht (HEISA-16/HEIS-KOTZ-12; Heidelberg scales of confidence regarding abstinence/controlled use) [35]	pre, post, follow-up
Satisfaction with the training	Fragebogen zur Beurteilung der Behandlung, Version Patient (FBB-P; Questionnaire for the satisfaction with treatment, patient version) with minor adaptations [36]	post
Peer resistance regarding cannabis use	own development	pre, post, follow-up

In addition, trainers were asked to answer a short questionnaire about themselves prior to t0 in order to gather data for analysing possible trainer effects in secondary analyses. This included their professional background, own beliefs and attitudes towards cannabis use and personality characteristics, using the Big Five Inventory-10 (BFI-10) [25].

